## Abstract

The number of patients with diabetes in Indonesia reach 19,47 million in 2021, mostly is caused by the adoption of sedentary and unhealthy lifestyles. Continuous self-management is important in diabetes care. It requires optimal coordination and communication between patients, families, and health care provider. The use of communication technology could be solution to the problem. This study aims to initiate an android-based mobile apps technology as a tool for patient, family, and healthcare provider to optimize patient with T2DM treatment. This study will be conducted in Public Health Centers (PHCs) in Yogyakarta using an exploratory sequential mixed-methods design which is divided into three phases. The first phase will use qualitative descriptive methods. Patients with T2DM, families, nurses, physicians and Health Social Security Agency officers in Indonesia will be involved in a focus group discussion (FGD) and in-depth interviews to understand their needs in optimizing the treatment. The second phase will be the development of an android-based application on the first phase results. The apps will be usability tested by involving experts (heuristic evaluation) and users (think aloud method) to ensure that the apps really meet targeted user’s need. In the third phase, we will collect feedback from user after using this apps for three months. The effectiveness of the apps will be measured by self-management improvement and glycemic control of patients with T2DM. The non-equivalent control group design will be applied using a pre-repeated post-test control group. The result of this study will be an Android-based Application which will be called Integrated Diabetes Self-Management (IDSM) app to optimize the implementation of diabetes self-management which can improve glycemic control of patients with T2DM as one of the indicators of the Indonesian Chronic Disease Management Program at PHCs.

## Introduction

### Background

The number of patients with diabetes in Indonesia reach 19,47 million in 2021 [1]. Type 2 Diabetes Mellitus (T2DM) is a metabolic disorder in which insulin secretion is impaired by pancreatic cells and the inability of insulin-sensitive tissues to respond to insulin [2]. The International Diabetes Federation (IDF) revealed that in 2019 the number of patients with diabetes was 463 million adults aged between 20 and 79 years and is likely to increase to 700 million by 2045 [3]. The number of patients with T2DM in Indonesia in 2013 was around 13% of the total population, and continues to increase from year to year [4].

The increasing number of patients with T2DM in Indonesia is caused by the sedentary and unhealthy lifestyles. Poorly managed T2DM has the potential to cause serious complications, like stroke, heart disease, kidney failure or chronic kidney disease (CKD), neuropathies such as blurred vision and other comorbidities, including diabetic ulcers [5].

Diabetes does not only demand immediate medical treatment but also continuous lifestyle changes that require patients to adapt both physically and psychologically in a long term, even for their entire lifetime. Patients with diabetes require holistic and integrative treatment as well as guidance and assistant to be able to manage them selves (good self-management) [6]. Diabetes self-management is an active behaviour in self-care to manage their disease. Patients with chronic diseases are responsible for the daily care of their illness during the time of illness and even for life [6, 7]. The goal of self-management is to normalize blood glucose levels and reduce the risk of long-term complications. Good glycemic control indicates successful short-term self-management [8].

Success in self-management is influenced by the compliance of patients with diabetes in managing their own disease. Adherence involves the patient’s voluntary and active involvement in the management of their disease. Compliance behaviour in patients with diabetes includes monitoring blood glucose at home, regulating daily food intake at home or in diet planning, managing home medications, performing recommended physical activities, and foot care. Compliance in the management of diabetes will have an impact on blood glucose levels stability within normal limits [9]. One study showed that the increase in HbA1c in patients was significantly associated with low adherence, low self-care knowledge and lack of contact with health care providers [10]. Non-compliance among patients with diabetes is more often due to lack of information, low awareness about diabetes management, few demands for daily action, emotional stress, low self-commitment and insufficient social support [6, 11, 12].

Social support in diabetes care can be provided by families and health workers. Continuous self-management is very important in diabetes care and requires optimal coordination and communication between patients, families, and nurses [13]. Family involvement to encourage patients with diabetes to adhere to medication, and to behave in a healthy way or modify their behaviour toward a healthier lifestyle is the key to success to control the disease [14]. Family has important roles in increasing patient’s independence and quality of life as well as in adapting back to society and regular social life in Indonesia [15]. The family cultural ethos that prevails in Indonesia is collectivist where family members are usually actively involved in caring for other family members who are sick [16, 17]. Self-management also requires proper support from nurses specially nurses that can enable patients to manage their diabetes confidently and competently. Nurses can facilitate and help patients to set goals and aid in problem-solving for diabetes management [18].

Low monitoring from families and nurses during the COVID-19 pandemic has caused metabolic regulation and control to be disrupted or inadequate so that hypertension and dyslipidemia often occur in patients with diabetes [19]. The existence of a universal protocol regarding social restrictions to minimize the spread of COVID-19 causes the health interventions provided to be considered more effective by using telehealth counselling or with a Smartphone application. This provides additional challenges for nurses to make an innovation by utilizing information technology (IT) in providing health services to patients with diabetes. The involvement of families and nurses through IT is very useful to help improve the self-management of patients with diabetes [20]. The novelty of this study is the development of an android-based application called ISDM which contains the pillars of T2DM management in one application which will connect 3 elements, in T2DM management patients with T2DM, families and nurses. The ability of this app connecting the 3 elements in one mobile application of T2DM management is the integration that never establish before in Indonesia.

### Study aims

The main aim of this study is to determine the effectiveness of an android-based IDSM application in self-management and glycemic control of patients with T2DM. The study’s specific aims are: 1) to explore perceptions about understanding, skills, barriers and needs of patients with T2DM, their families and nurses in using android applications to carry out diabetes self-management; 2) to develop an android-based IDSM application that can be used by patients with T2DM, their families and nurses; and 3) to determine the effectiveness of the application in self-management and glycemic control of patients with T2DM.

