Phase 3 (Quantitative study). This phase will use a non-equivalent control group design, which applies a pre-repeated post test control group design. Participants in this phase are Patients with T2DM, family caregivers, and nurses according to the inclusion criteria. The experiment and control group are determined by the person in charge of PROLANIS at PHC based on geographic location and PROLANIS activity evaluation data. Data collection will be conducted at two PHCs which has the lowest patients with T2DM number of visits based on data from BPJS Health. However, if the number is not sufficient, it will expand to other PHC. The experiment group will be given IDSM Application, and the control group will use the whatsapp group to communicate or consult directly with a health provider. Self-management will be carried out independently by the patient in his or her home. Monitoring by a health provider will be carried out using whatsapp group and when patient come to the PHC for routine check up. Determination of research subjects will be done by consecutive sampling on patients with T2DM. The sample size was calculated based on the formula for calculating sample size from Lemeshow by considering the hypothesis test for two populations means “two sided” test, with α = 5%; Z(1-α) = 1.96; β = 20%; Z(1-β) = 0,84, standard deviation = 0,9 with mean difference = 0.6 [26], then the calculation of the sample size is obtained n1 = n2 = 35 participants. To anticipate the possibility of participants dropping out, a number of samples will be added to keep them fulfilled by the formula: n’ = n/(1-f) [27]. As a result, four participants will be added so the number of samples needed is n1 = n2 = 39 participants. The sample will be divided into two groups, each group consisting of 39 patients with T2DM included in the experiment group and 39 Patients with T2DM included in the control group. The sample will be selected according to the inclusion criteria.

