## Expected results

Phase 1 (Qualitative study). The outcome of this study will be described through the themes found which will later be used as the content of the application software that will be developed. Phase 2 (Qualitative study). Based on the results of phase 1 and the literature review, we will develop an android-based IDSM Application that has been usability tested and can be readily applied. Phase 3 (Quantitative study), the main outcomes expected in this phase are the android-based IDSM Application that effectively improves self-management and glycemic control of Patients with T2DM.

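### Two unranked main outcomes share one sample size calculation that names neither: the stated 5% alpha is lost if either counts as success, and the stated 80% power if both are needed

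*Protocol article*

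**What the plan says.** Three places in the protocol article define what Phase 3 is meant to show, and each pairs the two outcomes:

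- *Study aims*: the main aim is to "determine the effectiveness of an android-based IDSM application in self-management and glycemic control of patients with T2DM". Specific aim 3 repeats the pair.
- *Abstract*: "The effectiveness of the apps will be measured by self-management improvement and glycemic control of patients with T2DM".
- *Expected results*: the main outcome hoped for in Phase 3 is an app that "effectively improves self-management and glycemic control of Patients with T2DM".

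No section calls one of them primary or says whether effectiveness needs one result or both.

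The sample size (*Study phases and data collection*, Phase 3) is a single "hypothesis test for two populations means “two sided” test" with "α = 5%; Z(1-α) = 1.96; β = 20%; Z(1-β) = 0,84" and "standard deviation = 0,9 with mean difference = 0.6". The result is that "the calculation of the sample size is obtained n1 = n2 = 35 participants". After an allowance for dropout, "four participants will be added so the number of samples needed is n1 = n2 = 39 participants". The sentence names no outcome and no unit.

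*Data analysis* gives each outcome its own between-group comparison: a summary measure (or Mann-Whitney) for the self-management score, and an independent t-test (or Mann-Whitney) on post-intervention HbA1c. It has no joint criterion and no test order.

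**The concern.** A 5% alpha and a 20% beta describe one test of one hypothesis. Here the conclusion, that the app is effective, rests on two tests, and the reader cannot tell which of them the 35 (39) per group was sized for. Nothing shows that the other is powered.

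The two outcomes differ in kind. One is a behaviour score taken monthly by research assistants, and the other is HbA1c at baseline and month 3. They may give different answers. If they do, the text leaves it open whether effectiveness is claimed or withheld, and that choice could be made after the results are known. *Dissemination and implementation* says that the findings will inform the national health insurer about using the app in its chronic disease programme, so the claim has practical weight.

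**Working it through.** **1. The plan's own figure.** Inputs from the Phase 3 text: difference 0.6, SD 0.9, z = 1.96 and 0.84.

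n per group = 2 × [0.9 × (1.96 + 0.84) / 0.6]² = 2 × 4.2² = 35.28.

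The plan states 35. Strict rounding up gives 36, which does not matter here. The dropout fraction is not stated. With an assumed 10%, 35 / 0.90 = 38.9, so 39, as stated. The calculation is thus one two-sided comparison with a standardised effect of 0.6 / 0.9 = 0.667.

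**2. Power of the sized outcome** (normal approximation): Φ(0.667 × √(n/2) − 1.96).

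- 35 completers per group: Φ(2.789 − 1.96) = 79.6%.
- All 39 per group complete: Φ(2.944 − 1.96) = 83.7%.

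**3. Success on either outcome, each tested at two-sided 5%.** Familywise error = 1 − P(|Z₁| < 1.96 and |Z₂| < 1.96). If the outcomes are independent, this is 1 − 0.95² = 9.75%.

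**4. Success only on both.** Type I error is at most 5%, because both tests must reject. If each outcome has 80% power, joint power = Φ₂(0.84, 0.84; ρ), where Φ₂ is the bivariate normal distribution function. Under independence it is 0.80² = 64%.

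| Assumed correlation | Familywise error (either) | Joint power (both, 80% each) |
|---|---|---|
| 0 | 9.75% | 64.0% |
| 0.3 | 9.5% | 66.6% |
| 0.5 | 9.1% | 68.7% |
| 0.8 | 7.8% | 72.9% |

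Under the either-rule, the chance of at least one significant result is never below the power of the sized outcome, so power is not harmed.

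**5. How far joint power depends on the second outcome.** The documents give no effect or SD for a second outcome.

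- Same standardised effect, independent: 0.796² = 63.4% with 35 completers and 0.837² = 70.1% with 39.
- Second outcome with an assumed 95% power, independent: 0.796 × 0.95 = 76% with 35 completers and 0.837 × 0.95 = 80% with 39.
- Upper limit, second outcome certain to be significant: 79.6% with 35 completers and 83.7% with 39.

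**6. Size needed under each rule** (both outcomes with standardised effect 0.667, 10% dropout assumed).

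| Rule | Per group | With dropout |
|---|---|---|
| One named primary | 35–36 | 39–40 |
| Either, alpha 0.025 each, 80% power per outcome | 43 | 48 |
| Both, 80% joint power under independence (√0.80 = 89.4% each) | 47 | 53 |

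**The case against.** *Data analysis* states no significance level. The 5% appears only as a sample size input, and an article may leave alpha allocation and test order to a fuller document. If the two outcomes are reported as two separate claims, 5% holds for each claim. The wording joins the outcomes with 'and', so a gain in self-management alone would not support the claim as written. The joint power figures are illustrations, and if the score is very likely to be significant, joint power approaches that of the sized outcome. The sample size sentence cites a source that may name its outcome.

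Much of this stands. The absence of a detailed multiplicity procedure is not the point. The point rests on what the text itself fixes: an unranked pair of main outcomes, and a full set of sample size figures tied to neither. Reading 'and' literally does not rescue the plan, because the stated 80% power then no longer describes the claim. The separate-claims reading is coherent, but the text speaks of one effectiveness verdict measured by both outcomes.

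A reader might also infer three things that the documents do not support:

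- That the score is a self-report that shifts easily. Trained research assistants measure it, with kappa testing planned, and nothing is said about how responsive it is.
- That 0.6 and 0.9 are HbA1c percentage points. This is possible, but it is not stated.
- That HbA1c must therefore be the primary. No section ranks it above self-management, which the app directly targets.

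**Conclusion.** The point holds, with one error rate lost under each success rule. A reader might infer that both alpha and power fail whichever rule applies. They do not: the either-rule breaks alpha and keeps power, and the both-rule keeps alpha and breaks power.

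- **Either suffices:** familywise error of about 7.8% to 9.75% instead of 5%, for an assumed correlation of 0.8 down to 0.
- **Both required**, the more natural reading: joint power of about 64% to 73% instead of 80%, over the same correlations and with an assumed 80% for each outcome. At the planned 35 completers per group it can never exceed 79.6%. It passes 80% only if nearly all 39 complete and the second outcome is almost sure to be significant.

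The correlations and the second outcome's power are assumptions, so the size of the loss is uncertain. Its direction is not. This should be settled before Phase 3 data are seen. It does not invalidate the design.

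**What to change.** 1. In the sample size text, state which outcome and unit the 0.6 and 0.9 describe.
2. Name that outcome as the single primary: month-3 HbA1c if that is the source of the figures, otherwise the self-management score with its summary measure defined. Test the other outcome at 5% only if the primary is significant. The stated alpha and beta then apply at essentially the present size.
3. Alternatively, keep both as co-primary, state that both must be significant, and restate the joint power as below 80% with the assumed effect, SD and correlation for each. Restoring 80% would take about 53 per group on the assumptions above.
4. In *Data analysis*, compare month-3 HbA1c between groups with adjustment for the baseline HbA1c already collected, in place of the post-only t-test. The groups are non-equivalent by design, so an unadjusted comparison of final values carries any starting difference into the result. Adjustment does not remove other differences between the health centers.

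**Cost.** A few sentences in the aims and sample size text, and a rewritten HbA1c analysis. No new measurements are needed, and options 2 and 3 need no meaningful increase in patients unless 80% joint power is wanted. The downside of option 2 is that the secondary outcome cannot support an effectiveness claim of its own if the primary is not significant. The downside of option 3 is a less favourable stated power.

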#### Aims of the study protocol

This protocol describes a mixed-method study using both qualitative and quantitative methods. This study aims to make an original contribution regarding integrated diabetes self-management by utilizing IT through an android application in improving self-management and glycemic control of patients with T2DM. Publication of the study protocol is the first step in the research process. The authors feel confident that this study protocol can be a reference for other researchers to get an overview of this study.

## Materials and methods

### Study design

This study will use an exploratory sequential mixed-methods design with three phases. The overview of this design is shown in the following Fig 1.

**Fig 1 pone.0277127.g001:**
[figure not shown]
The exploratory sequential mixed methods design.

This study is divided into 3 phases: qualitative, qualitative and quantitative methods. This study protocol has been approved by the Medical and Health Research Ethics Committee of the Faculty of Medicine, Public Health, and Nursing, Universitas Gadjah Mada with the number: KE/FK/1068/EC/2021 on September 27, 2021.

### Setting

This study will be conducted at Public Health Centers (PHCs) in Yogyakarta city. Yogyakarta city is one of the 5 districts in Yogyakarta Special Region Province. It has an area of 32.5 km2 (1,02% of the total Yogyakarta province area) and a population of 416,041 people in 2019. It is divided into 14 sub-districts. Every sub-district has 1 to 2 PHCs with a total number are 18 PHCs in Yogyakarta city [21]. Each PHC has a program to engage patients with chronical diseases in the disease treatment. The program is called program pengelolaan penyakit kronis shortened to “PROLANIS” which has 58–165 members with the same characteristics in all PHCs. PROLANIS could roughly translated as chronical disease management program.

### Study phases and data collection

The researcher will provide information both verbally and in writing about the purpose, benefits and possible side effects, confidentiality of information, consequence, freedom to refuse if they are not willing and can resign at any time during the study before the research get started. Finally, if participants are willing, then participants are asked to sign the consent form. Each participant has the right to refuse or discontinue participation at any time before or during data collection, without giving reasons.

Phase 1 (Qualitative study). The Focus Group Discussions (FGD) and in-depth interviews will be conducted for data collection. Participants will be divided into three groups, patients with T2DM, families and nurses group. Ten PHCs will be randomly selected, and participants will be selected by the person in charge in PROLANIS at each PHC according to the inclusion criteria. FGDs will be conducted to determine knowledge, abilities, barriers and needs of Patients with T2DM, families and nurses in carrying out diabetes self-management referring to the pillars of DM management. Specifically this phase will investigate targeted user’s need in using a mobile application. Patients with T2DM and families will be reached by staffs visiting their homes and being followed up by phonecall. The FGD will be held for approximately 60 minutes online using zoom video conference platform. It will be guided by researcher and assisted by two nurses with master’s degree qualification who act as note taker and observer. Gender, religion, and socioeconomic status are highly considered when we form the FGD groups to ensure that participants will feel comfortable expressing their unique experiences during the FGD process. We will triangulate the data collection by reviewing evidences from other sources to get accurate data. In-depth interviews will be conducted with 10 physicians who treats patients with T2DM at the PHC in Yogyakarta and are in charge at PROLANIS and 2 staffs in charge at the Health Social Security Agency namely [Badan Penyelenggara Jaminan Sosial Kesehatan (BPJS Health)] until data saturation is reached. The interview will be conducted by the researcher for 45–60 minutes in a closed room at PHC. Participant recruitment is determined by the person in charge of PROLANIS from the PHC. Participants will be given an explanation about the study and asked to complete informed consent forms for approval and willingness to participate in the study before the FGD and interviews are started. The FGD and interview guidelines were made based on references to self-management and the pillars of DM management. The FGD will be recorded using zoom recorder and interviews will be recorded using an audio recorder. FGD responses and interviews will be compiled in verbatim transcripts. Peer debriefing and member checking will be done to increase the trustworthiness of the data. We will ensure credibility by doing triangulation of methods (conducting FGD and interviews) and data sources (involving data from patients, families, nurses and physicians. To ensure transferability in this study we will later provide detail, clear, and systematic description of the research results.

Phase 2 (Qualitative study). Phase 2 is focusing on the apps testing. A Heuristic Evaluation (HE) technique will be conducted to ensure that the user interface and user experience of the apps are meeting all heuristic principles. HE is a usability testing that is needed before the application is used. Three experts who have experience in the field of computer science or digital health and understand the heuristic principles will conduct the evaluation in two rounds will be involved in two rounds [22, 23]. In the first round, each expert will conduct the evaluation independently. They will be asked to use the apps and note any violation on heuristic principles they found and rate each violation by 1 (cosmetic problem) to 4 (catastrophe). The apps’ module will be provided as wellas a Heuristic principles checklist. In the second round, after the evaluation is complete, a meeting will be arranged to discuss the identified heuristic problems and any disagreement among the experts. The result of the second round will be consensus on the heuristic problem and the rates.

The second technique is a Think Aloud (TA) method will be used to find any problem in the IDSM App. Participants in this phase are Patients with T2DM, families and nurses who were involved in the phase 1. Five participants in each group will be randomly selected [24]. They will be given an explanation and a consent form before the trial started. The TA method is based on the participants’ treatment-related responses as indicated by body posture and speech when evaluating with an integrated diabetes management application. Participants will be given a task in accordance with their role. Participants will be asked to say what they are doing, seeing, and thinking while they are using the apps to complete the given task. All the behaviour and words said by the participants will be audio visually recorded. Including the screen of the app. The recording will be compiled into a verbatim transcript. The results of the transcript will be analysed to find problems in the operation of the application software carried out by users [25].

Phase 3 (Quantitative study). This phase will use a non-equivalent control group design, which applies a pre-repeated post test control group design. Participants in this phase are Patients with T2DM, family caregivers, and nurses according to the inclusion criteria. The experiment and control group are determined by the person in charge of PROLANIS at PHC based on geographic location and PROLANIS activity evaluation data. Data collection will be conducted at two PHCs which has the lowest patients with T2DM number of visits based on data from BPJS Health. However, if the number is not sufficient, it will expand to other PHC. The experiment group will be given IDSM Application, and the control group will use the whatsapp group to communicate or consult directly with a health provider. Self-management will be carried out independently by the patient in his or her home. Monitoring by a health provider will be carried out using whatsapp group and when patient come to the PHC for routine check up. Determination of research subjects will be done by consecutive sampling on patients with T2DM. The sample size was calculated based on the formula for calculating sample size from Lemeshow by considering the hypothesis test for two populations means “two sided” test, with α = 5%; Z(1-α) = 1.96; β = 20%; Z(1-β) = 0,84, standard deviation = 0,9 with mean difference = 0.6 [26], then the calculation of the sample size is obtained n1 = n2 = 35 participants. To anticipate the possibility of participants dropping out, a number of samples will be added to keep them fulfilled by the formula: n’ = n/(1-f) [27]. As a result, four participants will be added so the number of samples needed is n1 = n2 = 39 participants. The sample will be divided into two groups, each group consisting of 39 patients with T2DM included in the experiment group and 39 Patients with T2DM included in the control group. The sample will be selected according to the inclusion criteria.

After participants are given an explanation beforehand, they will complete an informed consent forms, then they will provide sociodemographic data including religion, marital status, latest education, occupation, and income. The experiment group will first install the app, they will also get IDSM e-module and training how to use the apps before they actually using it. Meanwhile, the control group will only get e-modules. Measurement of diabetes self-management and HbA1C will be conducted before and after the intervention. The Indonesian Version- Diabetes Self-Management Instrument (IDN-DSMI 35) will be used to measure self-management of patients with T2DM. This instrument is valid and reliable with Cronbach’s Alpha values of 0.96 and 0.84–0.93 for the subscales. IDN-DSMI can measure self-management behaviour among Indonesian patients with T2DM at PHC [28]. Measurement of self-management scores will be done once a month for three months after the intervention both in the experiment group and in the control group. Based on Lally Gardner (2013), it takes 21 days to form a habit in changing behaviour [29]. The measurement of HbA1C will be conducted before and in the third month after the intervention both in the experiment group and in the control group. Two research assistants will be involved in measuring the self-management score of patients with T2DM. They will previously be given training to ensure the same understanding and perceptions among the to measure self-management and HbA1C. Kappa testing will be conducted to measure inter-rater reliability. The research assistants involved will be persons with minimum education of a bachelor’s degree in nursing. The flow of data collection in phase 3 is shown in the following Fig 2.

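### The PROLANIS person in charge decides which group gets the app, partly from programme-activity data, so in Phase 3 the choice of app site can favour one arm

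*Protocol article*

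**What the plan says.** All of this is in the protocol article, Materials and methods, Study phases and data collection, Phase 3, unless stated otherwise.

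- **Design:** "This phase will use a non-equivalent control group design, which applies a pre-repeated post test control group design".
- **Sites:** "Data collection will be conducted at two PHCs which has the lowest patients with T2DM number of visits based on data from BPJS Health". The plan then allows more: "However, if the number is not sufficient, it will expand to other PHC". It gives no rule for which PHC is added or to which arm.
- **Assignment:** "The experiment and control group are determined by the person in charge of PROLANIS at PHC based on geographic location and PROLANIS activity evaluation data".
- **Patients:** "Determination of research subjects will be done by consecutive sampling on patients with T2DM". The Phase 3 criteria under Study population are the same for patients in both arms.
- **Arms:** one arm uses the app and the other a WhatsApp group, so patients and staff can see which arm they are in.
- **Sequence:** explanation, consent and sociodemographic data come first. The text then turns directly to installing the app in the experiment group. It does not say when the assignment is made or disclosed.
- **Analysis (Data analysis section):** the arms are compared on HbA1c by an independent t-test on values after the intervention, with Mann-Whitney as the alternative. Multiple regression is planned to find the dominant variables and is not described as adjustment of the app effect.

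**The concern.** A non-randomised comparison depends on the arms being alike apart from the app. Here the assignment is made by someone who runs the programme in question. One of the two stated criteria describes how that programme is performing. A PHC with a more active PROLANIS may have patients who already manage themselves better, or who are about to improve. If the app goes to that PHC, the difference would be reported as an app effect. If it goes to the weaker one, a real effect could be hidden.

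The second route is recruitment. If staff and patients know the arm when patients are approached, willingness to join and judgements of eligibility (such as being able to operate a smartphone) can differ between the arms.

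The study's main aim is effectiveness, and under Dissemination and implementation the results are meant to inform BPJS Health about using the app. A built-in difference between the arms would therefore carry into that advice.

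**Working it through.** **1. The plan's own sample size.** Inputs from Phase 3: two-sided α 5% (z = 1.96), β 20% (z = 0.84), SD 0.9, difference 0.6.

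n = 2 × [0.9 × (1.96 + 0.84) / 0.6]² = 2 × 4.2² = 35.28 per group

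The plan states 35. The drop-out fraction is not stated, but 10% reproduces the final figure: 35 / 0.9 = 38.9, that is 39. The sample size is not at issue here and only supplies the scale.

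**2. Where the discretion lies.** Setting the statements side by side:

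| Decision | Who or what decides |
|---|---|
| First two PHCs | External rule (lowest T2DM visits, BPJS Health data) |
| Which group gets the app | PROLANIS person in charge, from location and activity data |
| Added PHCs and their arm | No rule given |
| Which patients | Consecutive sampling, common criteria |
| When the arm is disclosed | Not stated |

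The open decisions are the second, third and fifth.

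**3. What a shift between the arms would do.** Assume that the app has no effect and that assignment or recruitment alone makes the arms differ by b in the final outcome, in the app's favour. The values of b are assumptions: 1/6, 1/3 and 1/2 of the planned difference of 0.6.

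- SE = 0.9 × √(2/35) = 0.215; df = 68; critical t = 1.995
- Noncentrality = b / 0.215
- Result = P(t > 1.995) from the noncentral t distribution

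| Assumed b | b / SE | Significant in favour of the app |
|---|---|---|
| 0 | 0 | 2.5% |
| 0.1 | 0.46 | 6.7% |
| 0.2 | 0.93 | 14.8% |
| 0.3 | 1.39 | 27.9% |

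If the shift goes against the app, power at a true difference of 0.6 falls from 78.5% to 63.0% (shift 0.1) or 44.9% (shift 0.2).

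**4. Does a larger sample help?** No. By the normal approximation, the 0.2 shift gives 15.1% at 35 per group and 16.4% at 39. A fixed bias becomes easier to detect as an effect when n grows.

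**5. What a random draw changes with two PHCs.** Take an assumed site difference of 0.2. The two-sided rejection rate is 15.0% whether the app site is chosen or drawn. What changes is the direction. A choice that always favours the app gives 14.8% in its favour; with a draw, each direction has half of the total, 15.0% / 2 = 7.5%.

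**The case against.** Several points on the other side stand.

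- **The design is disclosed.** The plan calls it a non-equivalent control group design and will report under TREND, so non-random assignment is a declared feature. That is fair, but the label does not explain why programme staff should choose the app site from performance data.
- **Staff do not choose the sites.** A reader might infer that they do. The document does not support this for the first two PHCs, which come from visit counts held by BPJS Health.
- **Activity data are not the only criterion, and their use is not described.** Geographic location is named first, and a geographic split is a reasonable way to limit contamination. The activity data might serve to find comparable groups. The Setting section also says that PROLANIS members share the same characteristics across PHCs. It therefore cannot be said that the assignment builds in a difference, or in which direction; only that it can. If the PHCs really are alike, nothing is lost by drawing between them.
- **Foreknowledge of the arm is not stated.** A reader might take it as fact that every patient's arm is known before approach, consent and baseline. The text does not give the order, Fig 2 is not shown, and the remark that the sample will be divided into two groups can be read as sampling first. Foreknowledge is probable because both criteria read as site-level and no assignment step is described, but it remains an inference.
- **Hand-picking is limited.** A reader might picture a selected app arm against unselected controls. Consecutive sampling with common criteria argues against that. It does not prevent differential consent once the arm is known.
- **The sizes are assumed.** No figure in the plan gives the shift, and the outcome to which the SD of 0.9 belongs is not named.

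The analysis does not answer the point. A t-test on post-intervention HbA1c leaves any initial difference in place, and baseline adjustment would not remove selection on engagement or on a site's expected course.

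**Conclusion.** The point holds in a limited form. By the plan's own words, a person with an interest in the programme determines which group gets the app. That person uses data plausibly related to both outcomes, and no rule covers PHCs added later. The assignment is therefore not neutral, and it is probably not concealed from those who recruit.

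For scale, assumed shifts of 0.1 to 0.3 raise the chance of a false result favouring the app from 2.5% to about 7-28% (SD 0.9, 35 per group, no true effect). This illustrates how sensitive the comparison is; it does not estimate the bias in this study. The point should be addressed because the remedy is cheap. It does not show that the design is unusable or that the result will favour the app.

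**What to change.** Keep assignment by PHC, and replace the sentence on who determines the groups with wording such as:

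> Once all participating PHCs have been identified, including any added to reach the sample size, a researcher not involved in recruitment will assign them to app or control by random draw. The same information sheet will be used at all PHCs. Staff and patients will learn the assignment only after consent and baseline IDN-DSMI 35 and HbA1c are complete.

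Keep the non-equivalent control group label, and add that with one PHC per arm the draw removes deliberate choice and arm-aware recruitment but does not balance the arms or separate the app effect from the site effect.

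**Cost:** one draw and a wording change, with no extra patients or measurements. App installation must wait until baseline is complete at all PHCs. Phase 3 is planned at about three months, and follow-up alone takes three months, so the timeline must be extended to allow for the delay. PHC staff also lose their say over which site gets the app.
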